## Abstract

**Objective:**

This study aims to evaluate 1-year changes in functional status and aging-in-place (AIP)–relevant outcomes among homebound older adults receiving care through Korean Medicine home medical centers (KM-HMCs). The primary objective is to evaluate changes in activities of daily living measured by the Korean Activities of Daily Living (K-ADL) scale. Secondary objectives are to track major events (mortality, long-term hospitalization, and admission to long-term care facilities) and to examine factors associated with response.

**Materials and methods:**

This multicenter, prospective, registry-based observational study will be conducted at six KM-HMCs in South Korea. We aim to enroll approximately 250 participants aged 65 years or older with functional decline to obtain an analytic sample of about 200 after expected attrition. Participants will receive usual interprofessional home-based services. The primary outcome is the change in K-ADL from baseline to 1 year. Secondary outcomes include frailty assessed by the Korean version of the FRAIL scale, pain intensity assessed by a numerical rating scale, and AIP-related events. Analyses will use paired tests for changes over 1 year and multivariable logistic regression for factors associated with response, which was operationally defined as a decrease of ≥1 point in the K-ADL score from baseline to 1 year.

**Discussion:**

This registry will provide standardized longitudinal data on functional status and key events in a routine-care setting, addressing evidence gaps in Korean Medicine home medical care for AIP. Findings may inform evaluation and refinement of the KM-HMC model and guide future research and policy discussions.

## Introduction

South Korea is undergoing a rapid demographic transition toward an aged society [1]. In 2017, the proportion of people aged 65 years or older surpassed 14% of the total population, and by 2025 it exceeded 20%, marking Korea#39;s entry into a super-aged society [2]. Population aging has increased the burden of chronic illness and geriatric syndromes, while healthcare delivery remains largely oriented toward hospitals and long-term care facilities, limiting access to medical care for homebound older adults [3,4]. Given that long-term care services have historically emphasized institutional care and basic nursing support, frail older adults with mobility limitations often face barriers to timely and continuous medical care in the community [4].

Home-Based Primary Care (HBPC) supports longitudinal management of chronic conditions in patients’ living environments. Indeed, systematic reviews of HBPC programs for homebound older adults indicate associations with reduced hospital and emergency department use, lower healthcare costs, and high patient and caregiver satisfaction [5]. Concurrently, Aging in Place (AIP)—supporting older adults to remain at home while receiving appropriate medical and social support—has become a key policy objective [6]. In response, the South Korean government launched the Long-Term Care Home Medical Center (LTC-HMC) pilot program in late 2022. Under this program, designated home medical centers provide integrated HBPC for immobile or frail older adults enrolled in long-term care through interprofessional teams that typically include a physician or a licensed Korean Medicine doctor (KMD), a nurse, and a social worker. In this study, LTC-HMCs operated by Korean Medicine (KM) clinics are referred to as Korean Medicine home medical centers (KM-HMCs), where KMDs provide clinical care and participate in team-based service delivery, including KM interventions in home-based settings.

Despite the expansion of pilot services and early reports of favorable indicators [7], HBPC in Korea remains at an early stage of implementation, and evidence on longer-term outcomes and cost-effectiveness remains scarce. Furthermore, existing evaluations often lack longitudinal data on functional status, institutionalization, and quality of life [8]. Functional status, commonly assessed using activities of daily living (ADL), is a core outcome reflecting independence and care dependency [9]; yet, longitudinal evidence on ADL trajectories among frail older adults receiving KM-led HBPC is limited.

Therefore, we established a multicenter registry of KM clinics designated as LTC-HMCs and participating in the national pilot project. The primary aim is to evaluate 1-year change in ADL among homebound older adults with functional decline receiving HBPC from KM-HMCs. Secondary aims are to track AIP-relevant events (long-term hospitalization, admission to long-term care facilities, and mortality) and to explore patient- and service-related factors associated with these outcomes.

## Materials and methods

### Registry aims

The primary objective is to evaluate 1-year change in ADL among older adults with functional decline receiving care through KM-HMCs, measured using K-ADL. Secondary objectives are to: (1) track AIP-relevant events (long-term hospitalization, admission to long-term care facilities, and mortality); (2) assess 1-year change in frailty and chronic pain using the Korean version of the FRAIL scale (K-FRAIL) and the Numerical Rating Scale (NRS); (3) examine patient- and service-related factors associated with outcomes; (4) describe participant characteristics and services delivered; and (5) build a standardized longitudinal database to support ongoing evaluation and future research.

### Study design and setting

This is a multicenter, registry-based observational study collecting standardized baseline and follow-up data in routine practice; no study-mandated interventions or treatment restrictions will be applied. The protocol was prepared with reference to the SPIRIT (Standard Protocol Items: Recommendations for Interventional Trials) 2025 guidance, where applicable (S1 File. SPIRIT 2025 checklist).

The registry will be implemented at six KM-HMCs (Jungdong, Healthy Village, Dongbang Shintong Bubu, Haemalgeun, Kim Jeong-cheol, and Seohwa) participating in the national pilot project, selected to capture geographic variation. Under the pilot project, sites provide interprofessional home-based services that typically include at least monthly visits by KM doctors, twice-monthly nurse visits, and periodic social worker counseling.

KM-HMC services encompass comprehensive home-based primary care delivered in collaboration with community resources. In addition to Korean Medicine interventions (e.g., acupuncture, moxibustion, herbal medicine), services include a broad range of routine medical and nursing care such as wound care, catheter management, medication support, and monitoring of chronic conditions. Care is provided through coordination with local healthcare providers, nurses, and social welfare services, and may involve referral and linkage to community-based resources as needed. The specific components and frequency of care are individualized based on clinical judgment and patient needs.

### Participants and eligibility

Participants will be recruited during routine home visits. Written informed consent will be obtained from all eligible patients or their legal representatives prior to enrollment.

Eligibility criteria are age ≥ 65 years, current receipt of services at a participating KM-HMC, and Long-Term Care Insurance grade 3 or 4; grades 1–2 are not enrolled to focus on participants for whom 1-year changes in K-ADL can be feasibly assessed and interpreted in this registry.

Exclusion criteria are expected survival of <3 months or anticipated inability to complete 1-year follow-up, concurrent participation in other studies that may affect outcomes, acute conditions requiring immediate hospitalization, or severe cognitive or communication impairment precluding assessments even with assistance. Proxy responses will be permitted when direct responses are not possible; proxies will be limited to legal representatives or primary caregivers providing direct care for an average of ≥3 hours/day [10,11].

### Patient and public involvement

Patients and the public were not involved in the design, conduct, reporting, or dissemination plans of this study. Patient perspectives will be assessed using the Client Satisfaction Questionnaire (CSQ).

### Sample size

Because this is a registry-based observational study, the target sample size was set based on feasibility and the planned secondary analyses. Across the six participating sites, approximately 370 patients are expected to meet eligibility criteria. Assuming a participation rate of 70%, the registry aims to enroll approximately 250 participants. Allowing for 20% attrition due to mortality or institutionalization, the expected final analytic sample is approximately 200 participants.

For logistic regression of response, we prespecified response as a decrease of ≥1 point in the K-ADL score from baseline to 1 year. Because a validated minimal clinically important difference (MCID) for the K-ADL has not been established, this threshold was selected pragmatically, informed by indirect evidence from related basic ADL measures [12,13]. Based on this definition, we assumed a response rate of 35–45% according to a previous rehabilitation trial reporting recovery of ADL performance at 12 months [14]. With an expected final analytic sample of 200 participants, this would yield approximately 70–90 responder events, which is sufficient to support up to eight prespecified covariates based on an events-per-variable ratio of approximately 10 [15,16]. The prespecified covariates are age, sex, comorbidity count, baseline K-FRAIL, baseline K-ADL, Five Times Sit-to-Stand Test (FTSST), NRS, and service utilization, selected based on clinical relevance and prior evidence [17–20].

### Study procedures

The study timeline includes enrollment, baseline assessment, monitoring for 1 year, and a 1-year follow-up assessment (Fig 1). For new patients, baseline data are collected prospectively in the Case Report Form (CRF) at enrollment. For existing patients, the initial Comprehensive Assessment and Care Plan established at the commencement of home care services defines the start of exposure to the KM-HMC intervention; their current clinical status at enrollment is also recorded prospectively in the CRF. Throughout the study period, usual services will continue. Administrative records, including Comprehensive Assessments and Care Plans, and visit logs, are completed as part of routine practice; data from these records will be collected prospectively for new patients, while for existing patients, historical data will also be collected.

**Fig 1 pone.0347574.g001:**
[figure not shown]
SPIRIT schedule. * The official evaluation form mandated by the pilot project, updated annually. Data are collected prospectively for new patients and retrospectively for existing patients to retrieve initial baseline data.

### Outcomes

The primary outcome is the change in K-ADL from baseline to 1 year. K-ADL is a 7-item measure (score range 7–21), where lower scores indicate greater independence [18]. Secondary outcomes assessed at the 1-year interval include frailty status according to K-FRAIL (0: robust, 1–2: pre-frail, 3–5: frail) [17], changes in medication use (polypharmacy and deprescribing patterns), and patient satisfaction measured once at 1 year using the CSQ [21]. AIP indicators (mortality, long-term hospitalization >30 days, and admission to long-term care facilities) are recorded upon occurrence [22–24], while chronic pain intensity measured by the NRS (0–10) is assessed at every visit. Additional outcomes and covariates will be derived from pilot program–mandated administrative records, including the Comprehensive Assessment and Care Plan and visit logs, which capture sociodemographic characteristics, health and functional status, and service delivery details.

### Data collection and management

#### Data collection and quality control.

Data entry follows a two-step process: (1) completed paper CRFs and de-identified copies of relevant administrative records (study ID only) will be securely transferred to the Central Data Management Team at Dongshin University; and (2) the central team will check for completeness and consistency and enter the data into a web-based electronic CRF system (iClick, managed by the National Institute for Korean Medicine Development).

To reduce inter-rater variability and maintain consistency across sites, all evaluators will complete standardized training before study initiation, including standard operating procedures for K-ADL, K-FRAIL, and other assessments. Inter-rater reliability will be assessed early in the study. Data monitoring will be conducted by an independent, monitoring-trained KM doctor via on-site visits, which will include a comprehensive review of all source documents. To minimize attrition, staff will build rapport during regular visits and conduct prompt telephone follow-up after missed appointments to reschedule visits and address barriers to continued participation.

### Safety considerations

As an observational registry without experimental interventions, study-related risk is expected to be minimal. Mortality, long-term hospitalization (>30 days), and admission to a long-term care facility will be tracked as key events relevant to safety and sustainability. If such an event occurs, follow-up will be discontinued and the reason recorded in the CRF. Given the minimal-risk nature of the study, a formal data monitoring committee will not be convened; safety oversight will be conducted through regular investigator meetings and the independent monitoring process described above.

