### Statistical analysis

Analyses will be performed in R (version 4.5.2) using RStudio (version 2025.09.2). All tests will be two-sided with α = 0.05. Baseline characteristics will be summarized using descriptive statistics.

The primary outcome (change in K-ADL from baseline to one year) will be evaluated in the overall cohort using a paired t-test or Wilcoxon signed-rank test, depending on distributional assumptions. Because the registry includes both newly enrolled and pre-existing patients, baseline functional status and prior exposure to KM-HMC services may differ between participants. Baseline characteristics, including baseline K-ADL, will therefore be compared between newly enrolled and pre-existing patients. To assess the robustness of the findings in the presence of this mixed cohort structure, a sensitivity analysis will be performed using multivariable linear regression with change in K-ADL as the dependent variable, adjusting for baseline K-ADL, months of prior service exposure, and registration status (new vs. existing). No interim analysis is planned.

Longitudinal NRS (measured at each visit) will be analyzed using a linear mixed-effects model with a random intercept and time treated as a continuous variable. Other secondary continuous outcomes (e.g., K-FRAIL) will be analyzed using paired t-tests or appropriate non-parametric alternatives.

Factors associated with response will be examined using multivariable logistic regression, with response operationally defined as a decrease of ≥1 point in the K-ADL score from baseline to 1 year. Participants who die or are permanently institutionalized during follow-up will be classified as non-responders to reduce attrition-related bias. Prespecified covariates are age, sex, comorbidity count, baseline K-FRAIL, baseline K-ADL, FTSST, baseline NRS, and service utilization frequency. Model fit, multicollinearity, and influential observations will be assessed using standard diagnostics.

Missing data will be handled using multiple imputation by chained equations (MICE), creating 20 imputed datasets and including auxiliary variables related to health status and service use; estimates will be pooled using Rubin’s rules. Exploratory analyses using administrative data (e.g., service utilization patterns and detailed assessments) will be conducted for hypothesis generation, with methods selected according to the research question and data structure.

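### Follow-up stops at the first long hospital stay or facility admission, so later deaths and admissions go uncounted and living participants lose the one-year K-ADL

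*Protocol article*

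**What the plan says.** All references are to the protocol article.

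- **Safety considerations** names three key events: "Mortality, long-term hospitalization (>30 days), and admission to a long-term care facility will be tracked as key events relevant to safety and sustainability". The next sentence reads: "If such an event occurs, follow-up will be discontinued and the reason recorded in the CRF".
- **Registry aims** puts tracking of the same three events first among the secondary objectives. **Outcomes** lists them one by one: "AIP indicators (mortality, long-term hospitalization >30 days, and admission to long-term care facilities) are recorded upon occurrence". No composite and no first-event endpoint is defined.
- **Outcomes** makes one-year change in K-ADL, a seven-item scale, the primary outcome. **Participants and eligibility** allows proxy answers.
- **Statistical analysis** says, for the response model: "Participants who die or are permanently institutionalized during follow-up will be classified as non-responders". Missing data are to be multiply imputed.
- **Sample size** allows for 20% attrition from death or institutionalization, taking about 250 enrolled to about 200 analyzed.
- **Participants and eligibility** excludes patients with "expected survival of <3 months or anticipated inability to complete 1-year follow-up".

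**The concern.** Three indicators reported separately over one year each need observation for the full year or until death. Under the stated rule, observation ends at whichever event comes first. A death after facility admission, a facility admission after a long hospital stay, and a long hospital stay after facility admission all fall outside the data.

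Two further consequences follow.

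- A participant who is alive at one year after a non-fatal event has no one-year K-ADL because the rule stopped collection, not because the scale could not be completed. This missingness is tied to deterioration and falls on the primary outcome.
- The response model counts permanent institutionalization as non-response, but the stop is triggered by any facility admission or any stay beyond 30 days. Nobody looks afterwards, so permanence cannot be told from a stay that ended in a return home. Someone who recovers and goes home is neither dead nor shown to be permanently institutionalized. As written, that outcome would be imputed, leaning on participants who stayed under follow-up.

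**Working it through.** **1. The plan's own figure.** 250 × (1 − 0.20) = 200, as stated. If the 20% covers all three events (an assumption, since long hospital stays are not named there), about 50 of 250 have a first event. This count is the same with or without the stop. The article gives no split by event type and no risk after a non-fatal event, so everything below is illustration.

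**2. Missed deaths, first set of assumptions.** Suppose 20 to 30 of 250 have a non-fatal first event, spread evenly over the year; annual mortality afterwards is q = 30% to 50%; and 20 deaths occur as first events. With h = −ln(1 − q), the mean probability of death in the rest of the year is 1 − (1 − e^(−h))/h.

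- q = 0.30: h = 0.357, probability 0.159.
- q = 0.50: h = 0.693, probability 0.279.
- Lowest case: 20 × 0.159 = 3.2 missed deaths; 3.2/(20 + 3.2) = 14% of all deaths.
- Highest case: 30 × 0.279 = 8.36 missed deaths; 8.36/(20 + 8.36) = 29%.

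**3. Missed deaths, second set.** Assume constant competing hazards with a 20% one-year risk of any first event, so H = −ln(0.8) = 0.223. Let deaths be a share s of first events, and let the death hazard after a non-fatal event be m times the hazard before it. Then λd = sH, λn = (1 − s)H and μ = mλd. The probability of a non-fatal event followed by death within the year is the integral from 0 to 1 of λn·e^(−Ht)·(1 − e^(−μ(1 − t))) dt.

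| s | m | Deaths captured | True deaths | Missed per 250 | Share missed |
|---|---|---|---|---|---|
| 0.3 | 1 | 6.0% | 6.5% | 1.2 | 7% |
| 0.3 | 4 | 6.0% | 7.8% | 4.4 | 23% |
| 0.5 | 2 | 10.0% | 11.1% | 2.7 | 10% |
| 0.5 | 4 | 10.0% | 12.0% | 5.0 | 17% |
| 0.7 | 1 | 14.0% | 14.5% | 1.2 | 3% |
| 0.7 | 4 | 14.0% | 15.6% | 4.0 | 10% |

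These are crude counts over everyone enrolled. Censoring at the stop would put the m = 1 rows right, but not those with a raised hazard after the event.

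**4. Missed facility admissions.** Assume 25 non-fatal first events, 30% to 50% of them hospitalizations, and 20% to 50% of those later moving to a facility.

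- Low: 7.5 × 0.2 = 1.5 missed; 1.5/(17.5 + 1.5) = 8%.
- High: 12.5 × 0.5 = 6.25 missed; 6.25/(12.5 + 6.25) = 33%.

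**5. Living participants without K-ADL.** Under step 3, non-fatal first events number 50 × (1 − s), so 15 to 35. Subtracting the missed deaths leaves between 15 − 4.0 = 11 and 35 − 1.2 = 33.8, or about 4% to 14% of 250.

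**6. Entry exclusion, kept apart.** If the second clause covers prognosis, and 5% to 20% of otherwise eligible patients with a 40% to 80% event risk are kept out (assumed), the first-event risk in the wider group runs from 0.95 × 0.20 + 0.05 × 0.40 = 21% to 0.80 × 0.20 + 0.20 × 0.80 = 32%, against 20% in the cohort. This concerns whom the rates describe; the rates within the cohort are unaffected.

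**The case against.** The strongest reply is that the stop does less harm than it seems to. First-event incidence is fully observed in those enrolled. The aging-in-place events are secondary, and a single-arm registry has no treatment contrast to bias. The article mentions possible linkage to the national insurance database. Missing values are to be imputed, and deaths and permanent admissions count as non-response, so these people are not simply dropped from the response analysis. The full protocol, in the supplement, may define permanence and describe contact after an event.

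Much of this stands and limits the point. It does not remove it. The article lists separate indicators, not a first-event endpoint. Linkage is only a possibility, meant for secondary analyses, and consent to sharing is described as optional. Imputation cannot restore what a collection rule discards for a group whose course differs from the rest. A supplement that continued follow-up would contradict the rule in the article.

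The objection on size is also fair. The 14% to 29% range implies a death hazard after the event about four to eight times that before it; one- to four-fold gives 3% to 23%.

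A reader might also infer that the entry criterion biases the recorded event rates. The documents do not support that. An eligibility criterion changes whom the rates describe, not their correctness among those enrolled. Its wording is also ambiguous: if the second clause covered prognosis, the three-month survival limit would be redundant, which favors a non-prognostic reading such as a planned move.

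**Conclusion.** The point holds for events that follow a non-fatal first event and for the one-year K-ADL of survivors. One-year mortality and the separate event rates are biased low. Across both sets of assumptions, 3% to 29% of one-year deaths would be missed: 1.2 to 8.4 deaths, or 0.5 to 3.3 percentage points of 250. For facility admissions the illustrative range is 8% to 33%. The direction is firm for crude one-year rates; the size rests wholly on assumed inputs.

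It would be tempting to conclude that every aging-in-place rate is understated, or that the registry fails at its main purpose. Neither follows: the incidence of the first event is unaffected, and the primary objective is K-ADL change. The primary outcome is nevertheless touched directly, because living participants lose it by rule. The stop and the permanence condition in the response definition must be reconciled.

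**What to change.** **Safety considerations.** Amend the stop so that, after a non-fatal event, the registry still collects at one year: vital status, current residence, any later aging-in-place events and, if the participant is alive, K-ADL, by proxy where needed and with the mode of assessment recorded. This changes data collection only, not care.

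**If that is not done.** Redefine the endpoint as the first aging-in-place event, and do not report separate one-year mortality or admission rates as complete.

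**Statistical analysis.** Reconcile the permanence condition with the trigger for stopping. Residence at one year would supply the missing information.

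**Participants and eligibility.** Clarify whether the clause on completing a year covers prognosis, report how many are excluded on that ground, and state that event rates apply to the selected cohort. The criterion need not be deleted; doing so during recruitment would mix two entry populations.

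**Cost.** One brief contact for each participant with a non-fatal event, at most about 50 of 250 if no first event were a death, by staff who already visit and telephone participants. K-ADL taken by another mode may differ slightly, hence the record of mode. Enrollment began on November 5, 2025, so the first one-year point falls in November 2026. An amendment in force by then could still reach participants already stopped, provided their consent covers it. The last one-year point, October 20, 2027, falls within the planned data collection.
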